#### Exclusion criteria

Workers who are contraindicated to spa therapy or who underwent spa therapy within the last 12 months are not included. Nor are people with behavioral disorders or comprehension difficulties that make assessment impossible (Table 1).

**Table 1 Tab1:** MUSKA study eligibility criteria

Inclusion criteria
-Latent or symptomatic UE-MSD according to the SALTSA European consensus/INRS (French occupational health and safety agency) with a score on the Nordic questionnaire >2
-With or without a history of sick leave and working at the time of inclusion
-Age: >18 years <65 years
-Patient covered under national health insurance (person insured or dependent)
-Patient has given informed written consent to participate in the study
Non inclusion criteria
-Contraindication to spa therapy:
Unstable angina
Myocardial infarction within the previous 6 months
Cerebrovascular accident within the previous 6 months
Recent thrombophlebitis
Attack of inflammatory rheumatism
Progressive cancer
Vascular surgery within the previous 6 months
-Course of spa therapy within the previous 12 months
-Behavioral disorders or comprehension difficulties making assessment impossible

The research may be discontinued early if a contraindication to spa therapy or issues relating to participant availability arise. No exclusion period is planned in this study. No adverse effect is expected. Before each spa therapy session, the contraindications described in the non-inclusion criteria will be checked.

Travel expenses arising from participation in the study will be fully reimbursed at a fixed rate.

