### Research design

A prospective, multicenter, comparative (one intervention arm vs. one control arm), randomized (immediate vs. later treatment) study using Zelen’s design [25]. Workers randomized to the intervention group will be given a short, intensive, standardized spa therapy treatment during the following month. The intervention will be offered to control-group subjects at least 3 months later. The total duration of participation in the study for patients is 6 months. The centers were Clermont-Ferrand University Hospital/Royat spa center, Nîmes and Montpellier Hospital/Balaruc spa center.

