**Fig. 2 Fig2:**
[figure not shown]
Self administered questionnaires

Quantitative adherence (number and duration of sessions) and qualitative adherence (type and way of performing the intervention) will be systematically evaluated using monthly follow-up self-administered questionnaires [27, 28].

The assessment of endpoints on day 6 and then monthly over 6 months will be conducted by sending self-administered questionnaires by mail. Reminders and follow-up will be by mail and by telephone calls if necessary.

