#### Statistical analysis

Statistical analysis will be conducted on the intention-to-treat population using Stata software, V.13 (StataCorp, College Station, Texas, USA). A two-sided P value of less than 0.05 will be considered for statistical significance. Baseline characteristics will be presented for each randomized group as the mean ± standard deviation or median (interquartile range) according to the statistical distribution for continuous data, and as the number of patients and associated percentages for categorical parameters. Comparisons between randomized groups will be analyzed using the Chi2 or Fisher’s exact test for categorical variables and the Student t-test or Mann-Whitney’s test for quantitative parameters, with normality verified by the Shapiro-Wilk test and homoscedasticity by the Fisher-Snedecor test (notably for primary outcome QUICK DASH scale at 3 months). Primary analysis will be completed using (1) ancova taking into account baseline QUICK DASH as covariate as recommended by Vickers and Altman [29] and (2) linear regression model in multivariate context. Covariates used for adjustment will be fixed according to (i) univariate results and (ii) clinical relevance including (use of analgesics) stratification factors. Results will be expressed as effect sizes and 95% confidence intervals. Regarding the analysis of repeated measures, random-effect models (linear or generalized linear according to the statistical distribution of dependent variables) will be performed, as usually proposed, to study the fixed-effects group, time points, and “group x time” interaction, taking into account between- and within-subject variability. The impact of covariates (as observance) will be also studied. A sensitivity analysis will be performed to study the impact of missing data; when appropriate, they will be handled in accordance with the estimation method developed by Verbeke and Molenberghs [30].

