## Discussion

This randomized controlled trial is the first that will aim to evaluate multidisciplinary management of UE-MSDs using nonpharmacological treatment combining exercise, self-management, and spa therapy. The conduct of this study is important due to the absence of consensus or guidelines for the management of UE-MSDs and its medical and economic major issue. Moreover, despite numerous small scale studies, high quality scientific evidence for the efficacy of spa therapy for MSDs is lacking.

The mechanisms of action behind spa therapies in the treatment of pain are complex and as yet have only been partially elucidated. In workers with osteoarticular diseases, poultices and immersion in water have been shown to improve functional capacities and quality of life, and to lower the intensity of pain perceived [31–35].

Spa therapies induce mental relaxation, reduce anxiety, and so procure a feeling of well-being, which is an important factor in the prognosis of pain progression and chronic disorders because it improves quality of life [36, 37].

Exercising or being physically active must be the key element in chronic pain treatment, according to current recommendations [38]. Yet many obstacles to taking part in physical activities have been described in the literature, such as the fear of injury, pain, or misconceptions [39, 40] in this kind of population. The chronic nature of MSDs results in distorted thought processes often summarized by the general term catastrophism. Hence it is difficult to change the behavior of employees on partaking in physical activities. Workers thus need to be guided through a tailored, personalized care strategy, while adherence to treatment needs to be optimized. Information and education based on the biopsychosocial model are effective strategies for changing beliefs, minimizing repercussions, and increasing adherence to treatment. Thus, psychological counseling and self-management programs (which often happen in groups, for instance during spinal functional restoration programs in chronic lower back pain [41]) are primordial for developing adaptation strategies to reduce functional incapacity even if the pain is still present.

MSDs are one of the main causes of long-term sick leave, representing 34 and 17%, respectively, of sick leave in manual and nonmanual workers [42]. These periods of sick leave are a major economic cost to society [3].

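### Observance is measured after randomisation by self-report, so the secondary two-arm models should not adjust the group effect for it

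*Protocol article*

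**What the plan says.** The Statistical analysis section plans an intention-to-treat comparison of the arms, completed by an ANCOVA on baseline QuickDASH and a multivariable linear regression. For the repeated measures it plans random-effects models with group, time point and group-by-time interaction. The next sentence reads: "The impact of covariates (as observance) will be also studied". I take observance to mean adherence.

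Conduct of the study says what adherence covers: "Quantitative adherence (number and duration of sessions) and qualitative adherence (type and way of performing the intervention". Its source is the worker's own report, since both kinds "will be systematically evaluated using monthly follow-up self-administered questionnaires". The outcomes use the same kind of instrument and the same monthly rhythm: "The assessment of endpoints on day 6 and then monthly over 6 months will be conducted by sending self-administered questionnaires by mail".

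On exposure, Research design says that intervention workers "will be given a short, intensive, standardized spa therapy treatment during the following month", and then: "The intervention will be offered to control-group subjects at least 3 months later". Participation lasts 6 months. Under Intervention protocol, both arms receive the same exercise folder and follow a home programme. In the intervention arm the exercises are chosen individually during the treatment week, with supervised sessions. Controls get no such guidance at inclusion.

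**The concern.** Observance is a consequence of what happens after randomisation, not a characteristic the worker brings to it. Three features make it unsuitable as an ordinary covariate next to the group term.

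- The intervention may change it. One arm has supervised sessions and individually chosen exercises; the other has the folder alone. If adherence helps, adjusting for it removes part of the effect under test.
- It may share causes with the outcome. Workers with a worse outlook may exercise less and score worse on QuickDASH. Within one month the two can also drive each other.
- Up to about month 3, spa and supervised sessions exist only in the intervention arm, so any count that includes them overlaps with group.

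At stake is the reading of the secondary longitudinal models. An adjusted group coefficient could be reported as the treatment effect when it is not, or the observance coefficient could be read as the gain from adhering more.

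**Working it through.** The plan gives no figure for observance, so there is none to reproduce. What follows shows direction and possible size.

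**Inputs from Sample size determination:** SD 18, baseline 48, benefit of 12 points (effect −12, since a higher QuickDASH is worse), 75 per arm with 20% lost, hence 75 × 0.80 = 60 evaluable per arm. The standard error of the unadjusted difference is 18 × √(2/60) = 3.29.

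**Assumptions, not in the document:** an unmeasured trait U (SD 1) worsens QuickDASH with correlation *b* and lowers adherence with within-arm correlation *r* = 0.5. Mean adherence is *d* within-arm SDs higher in the intervention arm. Adherence itself has no effect on the outcome, so any observance slope is spurious.

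**Case 1: home-programme adherence, measured in both arms.**

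Spurious slope per SD of adherence = −18·*b*·*r* = −9*b*

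Adjusted group coefficient = −12 + 18·*b*·*r*·*d* = −12 + 9*bd*

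| *b* | *d* = 0 | *d* = 0.5 | *d* = 1 | Simulated, *d* = 1 (4,000 runs) |
|---|---|---|---|---|
| 0 | −12.0 | −12.0 | −12.0 | −12.0 |
| 0.3 | −12.0 | −10.65 | −9.3 | −9.2 |
| 0.5 | −12.0 | −9.75 | −7.5 | −7.6 |

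The unadjusted estimate stayed within 0.1 of −12 throughout. At *d* = 1 the squared correlation of group with adherence is 0.25/(0.25 + 1) = 0.20. The variance is inflated by 1/(1 − 0.20) = 1.25, and the standard error at *b* = 0 is 3.29 × √1.25 = 3.67 (simulated 3.68). The bias is zero if adherence is unrelated to prognosis or if the arms adhere equally.

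**Case 2: spa sessions (0 to 6), coded 0 for every control up to month 3.** The slope then comes from the intervention arm alone, and the group coefficient extrapolates to an intervention worker with no sessions. With attendance simulated around 5 sessions minus U plus unit noise, rounded and kept within 0 to 6, the adjusted group coefficient was −11.9, +2.5 and +12.2 for *b* = 0, 0.3 and 0.5, with a standard error of about 10. The spurious slopes were 0, −3.0 and −5.0 points per session. This is an extreme case, and the document does not say that observance would be coded this way.

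**Case 3: adherence has a real effect and no confounding.** If a share *m* of the 12 points runs through it, the adjusted coefficient is 12(1 − *m*): 9 points at *m* = 25%, 6 points at *m* = 50%. Both shares are assumed.

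**The case against.** The strongest reply is that the article says only that the impact of observance will also be studied. That wording can describe a separate or within-arm analysis, and a condensed article may leave the detail to a fuller document. This is possible. But the sentence calls observance a covariate and follows directly on the two-arm models, so entry into those models is the natural reading. The difficulty arises in any model that holds both terms.

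The second reply stands in full: the 3-month comparison and the baseline ANCOVA do not name observance.

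Some stronger readings are tempting but not supported:

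- *Spa exposure exists in one arm only.* This is true up to about month 3. Controls are then offered the same 6-day spa within their 6 months, and home adherence exists in both arms throughout. Since intervention workers have the spa in the first month, reports for months 2 and 3 should cover the home programme in both arms. The overlap in Case 2 therefore needs a cumulative or first-month count, and the document defines neither.
- *No valid exposure-response can be derived.* The article announces no such analysis, and exploratory or randomisation-based analyses remain possible.
- *The protocol itself says the intervention works through adherence.* The Discussion calls information and education "effective strategies for changing beliefs, minimizing repercussions, and increasing adherence to treatment", but as general background and as one of three benefits. Mediation is plausible from the design, not stated.
- *The spa centres already hold exact attendance.* The Exclusion criteria section says: "Before each spa therapy session, the contraindications described in the non-inclusion criteria will be checked". It does not say what is recorded, so nothing follows about attendance data.

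**Conclusion.** The point holds for the secondary models. If observance enters them beside group, the group and group-by-time coefficients no longer estimate the randomised effect, and the observance coefficient mixes any effect of adherence with prognosis and reverse causation. That conclusion needs only the timing and source of the measurement, and the possibility that adherence is affected by arm and related to outcome.

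The size is not determined by the document. The loss of about 3 to 4.5 of 12 points in Case 1 rests on an assumed prognostic correlation of 0.3 to 0.5, an assumed correlation of 0.5 between trait and adherence, and a 1 SD difference in adherence between arms. Smaller values give less bias, down to none. A reader might infer that the trial's main result is compromised; it is not. This is a cheap improvement to secondary analyses.

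**What to change.** In the Statistical analysis section, state that observance will not enter any model used to report the group or group-by-time effect, and that adjustment in those models is limited to baseline variables and stratification factors. Analgesic use, also named there for adjustment, would then mean use at baseline.

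Analyse observance separately. Define spa sessions and home programme apart, and report each as an exploratory within-arm association with QuickDASH, adjusted for baseline QuickDASH and labelled as confounded by prognosis. Using the preceding month's home adherence helps with time order but does not remove that confounding.

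If an effect in workers who attend the spa is wanted between arms up to month 3, use a complier-average estimate with randomisation as the instrument and state its assumptions.

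The cost is mainly a change of wording. The downside is that the adherence analysis uses one arm at a time and is less precise.

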## Discussion

This randomized controlled trial is the first that will aim to evaluate multidisciplinary management of UE-MSDs using nonpharmacological treatment combining exercise, self-management, and spa therapy. The conduct of this study is important due to the absence of consensus or guidelines for the management of UE-MSDs and its medical and economic major issue. Moreover, despite numerous small scale studies, high quality scientific evidence for the efficacy of spa therapy for MSDs is lacking.

The mechanisms of action behind spa therapies in the treatment of pain are complex and as yet have only been partially elucidated. In workers with osteoarticular diseases, poultices and immersion in water have been shown to improve functional capacities and quality of life, and to lower the intensity of pain perceived [31–35].

Spa therapies induce mental relaxation, reduce anxiety, and so procure a feeling of well-being, which is an important factor in the prognosis of pain progression and chronic disorders because it improves quality of life [36, 37].

Exercising or being physically active must be the key element in chronic pain treatment, according to current recommendations [38]. Yet many obstacles to taking part in physical activities have been described in the literature, such as the fear of injury, pain, or misconceptions [39, 40] in this kind of population. The chronic nature of MSDs results in distorted thought processes often summarized by the general term catastrophism. Hence it is difficult to change the behavior of employees on partaking in physical activities. Workers thus need to be guided through a tailored, personalized care strategy, while adherence to treatment needs to be optimized. Information and education based on the biopsychosocial model are effective strategies for changing beliefs, minimizing repercussions, and increasing adherence to treatment. Thus, psychological counseling and self-management programs (which often happen in groups, for instance during spinal functional restoration programs in chronic lower back pain [41]) are primordial for developing adaptation strategies to reduce functional incapacity even if the pain is still present.

MSDs are one of the main causes of long-term sick leave, representing 34 and 17%, respectively, of sick leave in manual and nonmanual workers [42]. These periods of sick leave are a major economic cost to society [3].

Having said that, the various treatments undertaken outside and within the work environment to keep workers at work or facilitate their return to work have their cost too [43]. A recent study evaluated the cost-effectiveness of three types of treatment for MSD aiming to facilitate the return to work of employees on long-term sick leave [42]. The interventions consisted of a physical activity and education intervention, a workstation intervention, or a combination of physical activity, education, and workstation assessment. This modeling approach showed that the most cost-effective intervention was physical activity and education. Given the current importance of the economic impact of chronic disorders and their treatment, our study will include a supplementary medical cost-effectiveness analysis with a societal perspective to evaluate whether it will be possible to implement our global multidisciplinary intervention [44]. Cost estimation will include direct and indirect medical costs. The cost of spa therapy will be calculated from guidelines of the French association of thermal centers. An economic analysis society’s willingness to pay for the thermal water treatment would be also measured.

The originality of this intervention lies, firstly, in its short, intensive format, which is compatible with remaining in work; secondly, in its multidisciplinary approach; and lastly, in its target population. The program is aimed at a population who are in employment at the time of treatment, so patients do not need to be on sick leave to follow treatment. This is made possible by the duration of the intervention (1 week), by the proximity of the centers to the workplace or residence of patients, and by the flexibility of treatment times relative to patients’ work schedules.

Inclusion of subjects commenced in September 2015 and will continue until February 2018. The study is projected to end in September 2018. Results should be available in February 2019.

This trial has the potential to demonstrate, with a good level of evidence, the benefit of combining exercise, a self-management program, and spa therapy in the therapeutic arsenal of UE-MSDs. In accordance with the literature, concerning exercise and education, we hope to show the benefits of a short course of spa therapy combined with a personalized self-management program on the functional capacity, pain, and quality of life of employees in their daily life. Standardizing the intervention will make it possible to develop and generalize a precise management plan that can be offered early to employees who present with these disorders when they consult a secondary care physician. This possible treatment may also be an alternative to keeping employees at work for occupational physicians forced to contend with the incapacities of their employees in the world of work [45].

## Abbreviations

MSD: Musculoskeletal disorder
UE-MSD: Musculoskeletal disorder of the upper extremities
